## Abstract

**Feasibility study:**

Objectives:Refine a bespoke enhanced support intervention (ESI) (including self-help materials, intervention manual and training) for implementation by community pharmacy (CP) staff to people with sub-threshold depression and long-term conditions (LTCs) based upon evidence-supported interventions in primary careDevelop and refine study procedures (recruitment strategies and set up, screening, participant recruitment, assessment, suitability of outcome measures and data collection procedures) for testing in the pilot study phase

Design: A case series/qualitative study

Setting: UK community pharmacy

Population: Adults with long-term health conditions who screen-positive for depression but who do not reach the threshold for DSM IV Moderate Depressive disorder

Intervention: Enhanced support intervention (ESI) delivered by an appropriately trained community pharmacy team member involving four to six sessions over four months. ESI is a modified form of an intervention within the collaborative care framework for sub-threshold depression validated in previous studies in UK primary care which appears suitable for implementation in community settings.

Sample size: 20–30 participants

Outcomes: Study implementation (recruitment and attrition rates), quality of data collection at baseline and 4 months and ESI adherence (number of contacts, DNA and drop out) as per objectives 1a/b

Qualitative evaluation: Semi-structured interviews with up to 10 participants and ESI facilitators and focus group(s) (range of pharmacy staff *n* = 8–10) will be conducted to explore the acceptability of the intervention and feasibility of the study, training and study procedures.

**External pilot study:**

Objectives:Quantify the flow of participants (eligibility, recruitment and follow-up rate)Evaluate proposed recruitment, assessment and outcome measure collection methodsExamine the delivery of the enhanced support intervention in a community pharmacy setting (intervention uptake, retention and dose) to inform process evaluationProcess evaluation, using semi-structured interviews with participants across a range of socio-economic settings, and pharmacy staff to explore the acceptability of the ESI within community pharmacy, elements of the intervention that were considered useful (or not) and appropriateness of study procedures

Design: Pilot randomised controlled trial, including a prospective economic and qualitative evaluation

Setting: As above

Population: As above

Intervention: As above with adaptations post feasibility study

Comparator: Usual care

Sample size: 100 participants

Outcomes: Data will be used to estimate recruitment, intervention delivery and study completion rates as per objectives 2a–d. Definitive estimates of the effectiveness of ESI will not be made.

Primary outcome: Depression severity (Patient Health Questionnaire 9) at four months.

Secondary outcomes: Patient acceptance, uptake and attrition. ICD10 depression status, anxiety (GAD 7), health-related quality of life (SF-12v2) and health-state utility (EQ5D 3L) will be measured at four months.

Economic evaluation: The incremental cost per QALY will be calculated from both the NHS and societal perspective.

Process evaluation: Using mixed methods, potential mediators/moderators of the intervention, the acceptability (to participants and pharmacy staff), barriers and facilitators to the use of ESI in community pharmacy, and impact on usual practice will be examined. Semi-structured interviews with approximately 30 study participants, 20 pharmacy staff and eight GPs near participating pharmacies will be conducted.

**Trial registration:**

ISRCTN: ISRCTN11290592

Protocol version number: Version 4.1 (dated 16th January 2018)

Study Sponsor Tees Esk and Wear Valleys NHS Foundation Trust

**Electronic supplementary material:**

The online version of this article (10.1186/s40814-019-0457-y) contains supplementary material, which is available to authorized users.

## Background

Depression accounts for 4.3% of the global disease burden and causes 63 million disability-adjusted life years annually. It is the largest cause of disease burden of all mental health problems and is set to become the highest amongst all health problems by 2030 [1]. Two to threefold increase in the prevalence of depression is found across the range of long-term conditions (LTCs) resulting in poorer outcomes, lower quality of life, a reduced ability to self-manage, substantial increased cost [2] and a significant contribution to health inequalities [3]. Sub-threshold depression, identified by a positive screen on the Whooley questions [4] and between two and four symptoms of depression, is highly prevalent and a major risk factor for progression to major depression [5]. Sub-threshold depression has comparable rates of associated excess mortality to major depression [6]. Estimates of the prevalence of sub-threshold depression in community samples range from 1.4 to 17.9% [7] and up to 20% in those people with LTCs. Clinical guidelines recommend brief psychological support [8]; however, psychological healthcare services struggle to meet demands of major depression and over 80% of ‘below threshold’ conditions remain untreated [9]. Psychological interventions reduce depressive symptoms in this population and reduce the incidence of major depression [10] but are not commonly available. Adopting a public health approach in at-risk groups such as those with LTCs may be an alternative to standard health services intervention; however, there is very limited evidence to support implementation.

Community pharmacies are ideally placed to offer opportunistic support to people with a range of health problems including low mood [11]. The Healthy Living Pharmacy programme is an example of extended roles of pharmacy teams, delivering for example smoking cessation and weight management interventions, through new innovative training programmes. These programmes lend support to the National Health Service (NHS) and Public Health England’s Five Year Forward View [12] calling for a radical upgrade in public health, including new partnerships that ‘break down barriers’ to support people with multiple health problems. The Marmot Review on Health Inequalities [13] recommended a focus on the mental health of people with long-term health problems due to the uneven socio-economic distribution and impact of such co-morbidities. The content of behavioural change/management approaches to sub-threshold depression shares much with other public health interventions such as smoking cessation or weight management (goal setting, facilitated self-help and diary keeping). Therefore, these interventions targeted at sub-threshold depression may also be suited to delivery by those staff delivering other public health behavioural change programmes. Given that 90% of people live within 20 min walk of their local pharmacy, especially within areas of high social deprivation [14] and with high rates of ‘footfall’ of people with LTCs, community pharmacies have a unique position to offer enhanced support for any co-morbid sub-threshold depression alongside other health promotion activities. High-quality evidence is needed to inform the design and delivery of such services. The Community Pharmacies Mood Intervention Study (CHEMIST) seeks to adapt ‘what works’ for people with sub-threshold depression in primary care and examine if this can be translated to the important public health setting of community pharmacy. This feasibility and pilot randomised controlled trial (RCT) study will address the potential for a behavioural change intervention and associated study procedures to work in this innovative public mental health setting in preparation for a definitive RCT. If this public health intervention is shown to have potential, a definitive RCT would also need to examine the depression prevention value of the intervention, which is of particular benefit to the individual, healthcare system and society [15].

Reviews of the literature indicate existing evidence is not sufficiently robust, or experience sufficiently developed, to support a definitive trial at this stage in the evolution of this public health intervention. CHEMIST therefore has two sets of objectives. The first set of objectives to be met in the feasibility phase is to refine our intervention (enhanced support intervention [ESI]) and research procedures. The second set of objectives to be met in the pilot RCT phase is to estimate study recruitment, acceptability and retention.

### Feasibility study objectives

Refine the bespoke enhanced support intervention (ESI) (including self-help materials, intervention manual and training) for implementation by community pharmacy staff for use with people with sub-threshold depression and LTCs based upon evidence-supported interventions in primary care.Develop and refine study procedures (community pharmacy set-up and recruitment strategies; participant screening, recruitment and assessment; suitability of outcome measures; and data collection procedures) for testing in the pilot RCT phase.

### External pilot RCT objectives

Quantify the flow of participants (eligibility, recruitment and follow-up rate).Evaluate proposed recruitment, assessment and outcome measure collection methods.Examine the delivery of the ESI in a community pharmacy setting (intervention uptake, retention and dose) to inform the process evaluation.Process evaluation, using semi-structured interviews with participants, pharmacy staff and general practitioners (GPs) across a range of socio-economic settings to explore the acceptability of the ESI within the community pharmacy setting, elements of the intervention that were considered useful (or not), and appropriateness of study procedures.

## Methods—feasibility study

### Design

A case series study with nested qualitative evaluation.

### Setting

Community pharmacies in the North of England

### Study population

Inclusion criteria: Adults (18+) with sub-threshold depression (screen positive with two to four depression symptoms confirmed by a diagnostic assessment tool) and one or more LTCs.

Exclusion criteria: People who have alcohol or drug dependence, or cognitive impairment, or have bipolar disorder/psychosis/psychotic symptoms, or are acutely suicidal, or those currently in receipt of psychological therapy.

### Recruitment

Recruitment to sub-threshold depression studies within community pharmacy is untested in the UK. Therefore, a key objective of the feasibility study will be to refine potential recruitment approaches to test in the external pilot RCT. Three approaches will be used.Pharmacy recruitment. Potential participants will be identified via medication use linked to LTC and/or other pharmacy use. They will be provided with a study information pack either directly, attached to home delivery prescriptions or via pharmacy mail outs.Publicity recruitment. Posters will be placed in community pharmacies, general practices and local community settings advertising the study with a central contact point for the study team. Interested people will be invited to contact the study team either by phone, email or via the study website.Primary care recruitment. General practice (GP) database searches will be used to identify potential participants (those with one or more LTC) and the study information pack will be mailed out by the practices.

The study information pack will include an invitation letter, a participant information sheet, a consent form, a background information sheet and a stamped addressed envelope for return to the study team.

These procedures will be refined in the feasibility phase to facilitate use and evaluation in the pilot RCT.

### Diagnostic confirmation

The Mini International Neuropsychiatric Interview (MINI) [16] will be used to establish the presence or absence of depression symptoms and disorder (sub-threshold/major depression). Diagnostic interviews will be carried out by a trained researcher over the telephone.

### Intervention

Enhanced support intervention (ESI): designed specifically for those with sub-threshold depression and LTCs to be delivered over four to six sessions in a 4-month period. Sessions will be delivered via telephone or face to face in the privacy of pharmacy consulting rooms. The ESI will be adapted from training/treatment materials used in previous sub-threshold depression research [17]. The ESI consists of four main elements.Behavioural activation (BA) focussed self-help support. A simple psychological approach focussed upon identifying life changes that have a detrimental impact on psychologically healthy activities and scheduling to stay well. This will be facilitated by a printed self-help workbook and supported by a trained pharmacy staff member (ESI facilitator).Proactive follow-up. Participants will be provided with a BA self-help workbook and an ESI facilitator would telephone/meet the participant at regular intervals to support its use.Symptom monitoring. The ESI facilitator will monitor symptoms at each support session using the depression scale from the Depression Anxiety Stress Scale (DASS) which is widely used/validated in a UK community context [18]. It is brief, simple to score, with clear clinical cut off scores (non/mild/moderate/severe).Decision supported signposting. Scores on the DASS will be used to guide decision-making by the ESI facilitator, guided by supervision delivered by clinical members of the study team. Where risk or significant clinical deterioration is noted, the participant would be supported to access more formal healthcare interventions.

The ESI will be delivered by pharmacy support staff (ESI facilitators) experienced in the delivery of extended roles (such as smoking cessation using behavioural change approaches) and/or training to Royal Society of Public Health standard (Understanding Health Improvement Level 2). Fidelity will be supported by ESI facilitator manuals and comprehensive face-to-face training adapted from those used in previous studies. In addition, a bespoke competency assessment will be used (based upon experience from previous studies) at the end of the intervention training to ensure ESI facilitators are able to support participants in the intervention. With participant consent, audio recordings of the intervention support sessions will be undertaken. A random selection of recordings (10–20%) across the different phases of the intervention (early/late) will be collected from each ESI facilitator and independently reviewed.

### Outcome measures

Depression severity will be measured by the Patient Health Questionnaire 9 (PHQ9) [19]. Widely used in clinical trials and settings, the PHQ9 provides excellent internal and external validity and specificity/sensitivity in a UK population [20]. The PHQ9 would be the primary outcome measure in a definitive RCT.

Secondary outcome measures will include prevention of depression (PHQ9 less than 10), anxiety (GAD7) [21], somatic symptoms (PHQ15) [22], quality of life (SF-12v2) [23], health-state utility (EQ5D-3 L) [24] and healthcare utilisation via an adapted version of the Adult Service Use Schedule (AD-SUS).

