#### Process measures

Moderators: depression severity (PHQ9), age of onset (MINI), number of episodes (MINI), LTC and socioeconomic status will be collected at baseline interview. Mediators: number of contacts, level of activation using the Behavioural Activation for Depression Scale (BADS) collected at treatment sessions [25].

Baseline demographic measures: DOB, ethnicity, education level, socioeconomic status and sex.

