### Study population

As described in the feasibility study above.

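### The secondary outcome 'prevention of depression' (PHQ-9 below 10) has no baseline condition, and entry sets no PHQ-9 limit, so it mixes remission and persistence with new onset

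*Protocol article*

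**What the plan says.** **Outcome.** Under Outcome measures (feasibility study), the article says: "Secondary outcome measures will include prevention of depression (PHQ9 less than 10". It attaches no condition on the baseline score. The pilot's Outcome measures section carries the list over and drops only the PHQ15.

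**Entry.** Study population requires "Adults (18+) with sub-threshold depression (screen positive with two to four depression symptoms confirmed by a diagnostic assessment tool". The exclusions end with "or are acutely suicidal, or those currently in receipt of psychological therapy", and none of them uses a PHQ-9 score. The confirming tool is the MINI, which "will be used to establish the presence or absence of depression symptoms and disorder (sub-threshold/major depression" (Diagnostic confirmation). For the pilot, the population is "As described in the feasibility study above".

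**Analysis.** The pilot's section on outcome and data storage and analysis summarises every secondary outcome descriptively by arm, with event counts and percentages for categorical ones. It names no subset at risk.

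**Baseline data.** Process measures lists, as moderators, "depression severity (PHQ9), age of onset (MINI), number of episodes (MINI), LTC and socioeconomic status will be collected at baseline interview". The baseline score is therefore available but is not tied to this outcome.

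**Related statements.** Background says that "a definitive RCT would also need to examine the depression prevention value of the intervention". The abstract's external pilot section lists ICD10 depression status at four months among the secondary outcomes, but the Methods outcome list does not.

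**The concern.** A prevention outcome needs people who are free of the event at the start. Here the event is a PHQ-9 score of 10 or more, while entry is decided on a MINI symptom count, and nothing in the article ensures that the two agree at baseline. An eligible person may already be at or above the cut-off. If that person drops below it, the outcome records prevention although the change is remission on that scale. If that person stays above it, the outcome records failed prevention although the state is persistence.

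What is at stake is the meaning of the figure. A reader planning the prevention part of a definitive trial would take this percentage as an estimate of how often depression develops. If people who start at 10 or above are more likely to be there at four months than the others, the figure overstates incidence. An arm difference could also come from remission alone, or from a chance difference in how many people started above the cut-off.

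**Working it through.** The article gives no figure for this outcome. Its only precision figure is for attrition, and it reproduces: 1.96 × √(0.20 × 0.80 / 100) = 0.078, the stated ±8 points. The relevant input from that section is the number measured, 100 × (1 − 0.20) = 80, about 40 per arm.

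**Step 1: can an eligible person start at 10 or above?** Assumptions, not in the documents: nine items scored 0 to 3, and a symptom corresponds to an item score of 2 or 3. For s symptoms the lowest total is 2s. The highest is 3s with all other items at 0, or 3s + (9 − s) with the others at 1.

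| Symptoms | Lowest | Highest, others 0 | Highest, others 1 |
|---|---|---|---|
| 2 | 4 | 6 | 13 |
| 3 | 6 | 9 | 15 |
| 4 | 8 | 12 | 17 |

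The symptom rule does not keep the baseline score below 10. This shows possibility, not frequency.

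**Step 2: what the pooled percentage measures.** Let q be the share starting at 10 or above, p the proportion of those still there at four months, and i the incidence among the rest. The documents give none of these.

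Pooled share at 10 or above = q·p + (1 − q)·i

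- Low end (q = 20%, p = 50%, i = 10%): 0.10 + 0.08 = 18%.
- High end (q = 50%, p = 60%, i = 20%): 0.30 + 0.10 = 40%.
- Middle illustration (q = 40%, p = 60%, i = 15%): 0.24 + 0.09 = 33%, against an incidence of 15%.

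The excess over incidence is q·(p − i). It is positive only if p is larger than i, and it vanishes as q goes to 0.

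**Step 3: how much of the reported 'prevention' is remission.** Keep p = 60% and i = 15%. The share below 10 at four months is then (1 − q) × 0.85 + q × 0.40.

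| q | Reported below 10 | Among those at risk | Remissions among those reported |
|---|---|---|---|
| 10% | 80.5% | 85% | 0.04 / 0.805 = 5% |
| 20% | 76.0% | 85% | 0.08 / 0.76 = 11% |
| 40% | 67.0% | 85% | 0.16 / 0.67 = 24% |

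**Step 4: arm differences without a prevention effect.** Suppose incidence is equal in both arms, but remission is 40% in one and 60% in the other. The outcome then differs by q × 0.20, which is 4 points at q = 20% and 8 points at q = 40%. Chance imbalance also acts. With 40 per arm, the arm difference in the share starting at 10 or above has standard deviation √(2q(1 − q)/40), which is 8.9 points at q = 20% and 11.0 at q = 40%. Each point of imbalance shifts the outcome by 0.85 − 0.40 = 0.45 points.

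**The case against.** The strongest reply is that the article never says the outcome is scored in everyone. It gives a cut-off and says that secondary outcomes are summarised by arm. The denominator could be restricted in a full protocol or analysis plan that is not shown. That limits certainty about what will be done. It does not mend the published definition, which labels a follow-up cut-off as prevention with no baseline condition.

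It is also fair that the magnitude is assumed throughout and that the outcome is a descriptive secondary one in a pilot that disclaims definitive effectiveness estimates. Both points stand and hold the consequence down.

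A reader might infer three stronger things, none of which the documents support:

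- **That this is the pilot's only prevention-type outcome.** The abstract also lists ICD10 depression status at four months, a natural measure of onset in people who enter below the diagnostic threshold. Its absence from the Methods list is an inconsistency to settle.
- **That nothing remains to be prevented in someone who starts at 10 or above.** By the protocol's own entry definition, that person is still sub-threshold on the MINI, and progression to major depression can still be prevented. Only the PHQ-9 event has already occurred.
- **That the definitive trial would be undersized because of this percentage.** The article names PHQ-9 severity as the definitive trial's primary outcome and looks to the pilot for its standard deviation, attrition and recruitment. It does not say that this percentage will size anything.

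**Conclusion.** The definition is wrong as written. On the plain reading of the outcome, entry and analysis sections, people who start at 10 or above are included, so the percentage is a mixture and not a measure of prevention. For those who start below 10, it measures absence of the event at one time point, so the fault lies in the pooling and the label.

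The pooled event rate overstates incidence if a material share start at 10 or above and they persist more often than others become new cases. That share is not given, so the size is unknown. The 18-40% range rests wholly on the assumed inputs, and the possibility of starting at 10 or above rests on the assumed item scoring and its match to MINI symptoms. The consequence is modest, and lies mainly in what the figure would be taken to mean when the prevention question is planned.

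**What to change.** - Define the outcome as PHQ-9 of 10 or more at four months among participants below 10 at baseline.
- Report PHQ-9 below 10 at four months among those at 10 or above at baseline separately, as remission on that scale.
- Show the two-by-two table of baseline by four-month status for each arm.
- State how this outcome relates to ICD10 depression status, and make the abstract and the Methods list agree.
- At minimum, rename the outcome PHQ-9 below 10 at four months and drop the word prevention.

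The cost is one sentence and one table, from data already collected. The drawback is precision. If 10-40% of the 80 measured start at 10 or above, the at-risk set is 80 × 0.90 = 72 down to 80 × 0.60 = 48. With 48 at risk and 15% incidence, about 7 events are expected (48 × 0.15 = 7.2). The Wilson 95% interval for 7/48 is about 7% to 27%, so the estimate would answer the right question but remain imprecise.
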